### Blinding

2.6

Patients and staff are not blind to the treatment condition.

### Outcome measures

2.7

Primary outcome measures comprise of subjective sleep quality by using the PSQI and sleep duration measured by actigraphy recordings. To assess changes in subjective sleep quality the PSQI global value is computed as proposed by the authors (Buysse et al., 1989). Sleep duration is measured by using sleep diaries completed by the participants and by monitoring TST with actigraphy.

Secondary outcome measures are composed of daytime sleepiness, which is quantified as the global score of the ESS-CHAD (Janssen et al., 2017). Further actigraphy dependent outcome measures are outlined in an additional study protocol.

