**Method:**

The study plans to investigate the efficacy of the intervention using a waitlist control design. A sample of children and adolescents (aged 10–18 years) that are undergoing treatment for psychiatric disorders in day treatment centers in Kiel and Rostock, Germany, will be included. Sleep quality is assessed using the Pittsburgh Sleep Quality Index. Sleep duration is assessed by using a sleep diary completed by the patients and as well using actigraphy as an objective measure. Analysis of variance will be used to detect treatment effects. Secondary outcomes include variables regarding sleepiness.

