### Sample size calculation

2.4

The sample size was computed assuming a repeated measures ANOVA with a within-between interaction using g*Power 3.1 (Faul et al., 2009) with the sleep duration used as primary outcome measure. We assumed a middle effect size (*d* = 0.25), a power of 0.90 and an alpha-error of 5%. This resulted in a minimum sample size of *N* = 46 participants. As we expect a drop-out rate of about 25%, the target enrollment is 60 participants.

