### Data analysis

2.9

The study is conducted using a control design in which the control group receives regular group therapy. To detect treatment effects, variance in between intervention and control group at T0 and T1 (see Figure 1) is assessed by using a repeated measures ANOVA including two factors (GROUP and TIMEPOINT). Significance level is set to be at *p* = 0.05. Post-hoc tests will clarify effect size and direction. If statistical assumptions are not met, non-parametric alternatives will be used. In additional exploratory analyses we plan to account for sociodemographic aspects or the influence of different diagnoses for the efficacy of the program.

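### Section 2.4 sizes the trial on one primary outcome at 5%, but section 2.7 names two: if either alone may establish efficacy, the familywise error is about 9–10%; if both must, joint power is about 0.83

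*Protocol article*

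**What the plan says.** - **Protocol article, 2.4 Sample size calculation.** The trial is sized "with the sleep duration used as primary outcome measure". The instrument is not named. The inputs are given as "We assumed a middle effect size (*d* = 0.25), a power of 0.90 and an alpha-error of 5" per cent, leading to a minimum of 46 participants and a target enrolment of 60.
- **2.7 Outcome measures, first sentence.** "Primary outcome measures comprise of subjective sleep quality by using the PSQI and sleep duration measured by actigraphy recordings".
- **2.7, same paragraph.** "Sleep duration is measured by using sleep diaries completed by the participants and by monitoring TST with actigraphy". The secondary list in 2.7 contains only daytime sleepiness, and the exploratory aims in 1.1 name sleep onset latency and sleepiness. Diary duration is therefore not placed in any tier.
- **Abstract, Method.** "Sleep duration is assessed by using a sleep diary completed by the patients and as well using actigraphy as an objective measure". Neither instrument is ranked above the other.
- **2.9 Data analysis.** The analysis is a group-by-timepoint repeated measures ANOVA on T0 and T1. "Significance level is set to be at *p* = 0.05". Direction is handled afterwards: "Post-hoc tests will clarify effect size and direction".

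**The concern.** The article gives two accounts of what the primary outcome is. Section 2.4 has a single outcome, and its N and alpha belong to a single test. Section 2.7 has two outcomes, and 2.9 sets one 0.05 level for the analysis.

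How far the printed design figures still hold depends on how the two results combine into a conclusion. If one significant result is enough, the overall error is no longer 5%. If both are needed, the overall power is no longer 0.90. Only a rule that puts one outcome first leaves both figures standing.

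A decision hangs on this: section 3.2 makes release of the manual and materials conditional on the intervention proving efficacious. A combination rule chosen after the results are known would not be credible.

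**Working it through.** **1. Reproducing the stated N.** For the within-between interaction of a repeated measures ANOVA, the noncentrality parameter is λ = f²·N·m/(1 − ρ), with 1 and N − 2 degrees of freedom for two groups and m = 2 timepoints.

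Inputs from 2.4: effect 0.25, alpha 0.05, power 0.90. The groups and timepoints come from 2.9. Two inputs are assumptions: 0.25 is read as Cohen's f, although it is printed as d, and ρ = 0.5 for the within-person correlation, which the article does not give.

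- N = 46: λ = 0.0625 × 46 × 2 / 0.5 = 11.5; power 0.912.
- N = 44: λ = 11.0; power 0.8997, just short of 0.90.

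So N = 46 is reproduced for **one** test at 5%. The result depends on ρ: the required N is 62 at ρ = 0.3 and 28 at ρ = 0.7. Reading 0.25 literally as d (f = 0.125) gives N = 172 at ρ = 0.5. That is a separate matter and is not pursued here.

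**2. If either named primary suffices.** The chance of at least one significant result when neither outcome is affected, with each test two-sided at 0.05, is 1 − 0.95² = 0.0975 for independent tests. The correlation r between the two test statistics is not in the article, so a range is shown. The favourable-direction figure under independence is 1 − 0.975² = 0.0494, against 0.025 for a single test.

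| r | any significant result | favourable direction only |
|---|---|---|
| 0 | 9.75% | 4.9% |
| 0.3 | 9.5% | 4.8% |
| 0.5 | 9.1% | 4.5% |
| 0.7 | 8.4% | 4.2% |
| 0.9 | 7.0% | 3.5% |

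**3. If both are required.** The error is at most 5%. With f = 0.25 on each outcome and ρ = 0.5, joint power at N = 46 under independence is 0.9125² = 0.833. With positive correlation between the tests it rises, approaching 0.912 only when they are almost perfectly correlated.

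**4. If alpha is shared over the two outcomes.** At 0.025, the first Holm step, power for one outcome at N = 46 is 0.854. Restoring 0.90 at that level takes N = 54, or 54/0.75 = 72 enrolled. Under Holm, 0.854 is a floor for a given outcome, because once one outcome passes the other is tested at 0.05.

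**5. If one outcome is tested first.** With actigraphy total sleep time at 0.05 and the PSQI at 0.05 only after success, the familywise error stays at 5% and power for total sleep time stays at 0.912. The chance of also claiming the PSQI is the joint figure from step 3, about 0.83 under independence.

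**The case against.** **The success rule may be in a document not shown.** This is a condensed article, and a multiplicity rule is often left to the analysis plan. That stands: the lack of a rule here is not in itself an error. But one primary in 2.4 and two in 2.7 are both printed. It can be said that 2.4 merely sizes on one of two primaries and does not call it the only one. Even so, the printed alpha and power then describe only part of the primary analysis, and the text should say so.

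**Either-suffices is not stated.** Correct. The hypotheses in 1.1 and in the Conclusion join better quality and longer duration with an *and*, which leans towards requiring both. The text does not make this a criterion either. The 9–10% is therefore conditional, and a reader who took it as the trial's error rate would go further than the documents allow.

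**The rate is two-sided.** Also correct. The F test has no direction, and a significant worsening would not be called efficacy. In the favourable direction the error is about 5% against 2.5%. The absolute figure is half as large; the near-doubling remains unless the tests are highly correlated.

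**A 14% error rate.** A reader might count diary duration as a third primary and reach 1 − 0.95³ = 14.3%. The documents do not support this. The first sentence of 2.7 ties the primary to actigraphy, and the diary sentence describes measurement without calling the diary primary. The figure also needs independence, although diary and actigraphy measure the same quantity; at r = 0.5 it is 12.5% and at r = 0.9 it is 8.4%. What stands is that the diary's tier is unclear.

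**Self-report as the likely route to a claim.** A reader might infer, since 2.6 says patients and staff are unblinded, that a claim would most likely come through the PSQI. The article gives no expected effect for the PSQI, so this cannot be calculated. It is a question of bias, separate from the error rates above.

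**Conclusion.** The point holds in conditional form. Sections 2.4 and 2.7 disagree on how many primary outcomes there are, and N = 46 with alpha 5% and power 0.90 is right for one test only.

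- **Either primary suffices, unadjusted:** two-sided familywise error about 9–10%, falling to 8.4–7.0% at correlation 0.7–0.9; about 5% instead of 2.5% in the favourable direction.
- **Both required:** error controlled, joint power about 0.83 under independence.

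The error rates assume that each test holds its nominal 5%. The power figures assume f = 0.25 on each outcome and a within-person correlation of 0.5. The article does not say which of the two cases applies, so neither consequence can be stated as the trial's actual property.

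**What to change.** Reconcile 2.4 and 2.7, name the instrument for sleep duration in 2.4, and state one rule before data are seen.

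**Preferred:** make the T0–T1 comparison of actigraphy total sleep time the first test at 0.05. Test the PSQI global score at 0.05 only if that test is significant, and list diary duration as secondary. The stated N and alpha then stand. The cost is a few sentences in 2.4, 2.7 and 2.9, and the PSQI alone can no longer establish efficacy.

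**Alternatives:**
- Holm across total sleep time and PSQI, with power restated at the 0.025 first step (about 0.85 at N = 46; N = 54 to restore 0.90).
- Both required, which is closest to the wording of the hypotheses, with joint power restated (about 0.83 at N = 46 under independence).

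Each alternative costs some of the stated power, or a larger sample.

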### Data collection and management

2.8

Pseudonymized data is collected after informed consent is obtained. Questionnaires and sleep log data is collected using paper and pencil and later digitalized under said pseudonymized study code. Sensitive personal data is only accessible by the personnel conducting the study in the specific day clinic and will not be shared between the participating facilities. All digital data including actigraphy is stored under the described study code locally during the duration of the intervention before being anonymized and uploaded to be shared between the participating centers. The upload is conducted to CAU-Cloud, the cloud system provided by the Christian-Albrechts-University in Kiel (CAU), which is secured by the local IT protocols and therefor sufficient to protect study data.

### Data analysis

2.9

The study is conducted using a control design in which the control group receives regular group therapy. To detect treatment effects, variance in between intervention and control group at T0 and T1 (see Figure 1) is assessed by using a repeated measures ANOVA including two factors (GROUP and TIMEPOINT). Significance level is set to be at *p* = 0.05. Post-hoc tests will clarify effect size and direction. If statistical assumptions are not met, non-parametric alternatives will be used. In additional exploratory analyses we plan to account for sociodemographic aspects or the influence of different diagnoses for the efficacy of the program.

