### Study sample and setting

2.2

The study is conducted as a multicenter-study in three day clinics for children and adolescent psychiatry in northern Germany. Participating clinics comprise of the day clinic facility of the Clinic for Child and Adolescent Psychiatry, Psychotherapy and Psychosomatics at the Center for Integrative Psychiatry, School of Medicine in Kiel and the two day clinics of the Department for Child and Adolescent Psychiatry and Neurology at the Rostock University Medical Center in Rostock. All patients and parents/custodians receive age-appropriate information about the study procedure and the collection of data. The collection of study data is only possible if written informed consent is granted by both, children and parents/custodians. Depending on the facility, groups consist of different age ranges overall ranging from 10 to 18 years. Age-related differences regarding time needed to fill out questionnaires and worksheets are accounted for by personnel to ensure the programs practicability across all age groups. Groups may vary in size depending current treatment capacity. Inclusion criteria for this study are rather limited: To take part in the study the patients need to be between 10 and 18 years old, being treated in the facility consistently for the whole duration of the study and need to be able to comprehend presented concepts such as time. Further a sufficient understanding of the German language as well as the ability to read and write short phrases is required. Patients that do not consent to their data being processed take part in the intervention nevertheless. They fill out the questionnaires and sleep logs relevant to the intervention, but those will not be collected for analysis and no actigraphy will be recorded.

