### Randomization

2.5

Intervention and control group run in alternating turns. Patients are assigned to the condition and undergo the study procedure as scheduled for the condition as soon as enough patients were admitted to the day patient department. After one group completes the intervention, a break of 8–10 weeks follows, after which the other group begins (i.e., after an intervention group and the described break a control group follows) Therefor participants are quasi-randomized into their assigned condition. This process is repeated until the estimated sample size is met.

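### Condition is assigned to whole clinic cohorts, but the planned ANOVA and the N = 46 calculation treat participants as independent, so the 5% error rate is not assured and the stated 90% power does not hold for a cohort-level test

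*Protocol article*

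**What the plan says.** Section 2.5 (Randomization) states: "Intervention and control group run in alternating turns". Section 2.1 and the legend of Figure 1 give the detail. A 28-day group in one condition is followed by a pause of 8 to 10 weeks and then by a group in the other condition. A patient's condition follows from when treatment at the facility began. Sessions are held in groups in both conditions, at three day clinics. On group size, section 2.2 says only: "Groups may vary in size depending current treatment capacity".

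Section 2.9 (Data analysis) fixes the test: variance between the conditions at T0 and T1 "is assessed by using a repeated measures ANOVA including two factors (GROUP and TIMEPOINT"). GROUP here means condition. No term for therapy group, turn or clinic is named. The threshold is given as "Significance level is set to be at *p* = 0.05".

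Section 2.4 uses the same framework: "The sample size was computed assuming a repeated measures ANOVA with a within-between interaction using g*Power 3.1". Its inputs are "We assumed a middle effect size (*d* = 0.25), a power of 0.90 and an alpha-error of 5"%, and "This resulted in a minimum sample size of *N* = 46 participants".

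**The concern.** The unit of assignment is the cohort, and the unit of analysis is the patient. Members of a cohort share the condition, the clinic, the calendar weeks and the group sessions. Anything that moves a whole cohort's sleep between T0 and T1, such as a school holiday or the way one group's sessions went, enters the planned test once per member as if it were separate evidence.

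Two things follow. The standard error of the interaction can be too small, so the nominal 5% is not assured. And the 90% power belongs to a test with 44 error degrees of freedom, whereas a test based on cohorts has only the number of cohorts minus two. This affects the test of both primary outcomes, PSQI and sleep duration. According to section 3.2, the result decides whether the manual is offered to other professionals.

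**Working it through.** **1. The plan's own figure.** With two conditions and two time points, G*Power's within-between interaction uses λ = f² × N × m/(1 − ρ), with 1 and N − 2 degrees of freedom. N = 46 appears if the stated 0.25 is read as Cohen's f and ρ = 0.5. The article labels the effect d and gives no correlation, so both are assumptions.

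- λ = 0.0625 × 46 × 2/0.5 = 11.5, and power = 0.912.
- N = 44 gives 0.8997, so 46 is the smallest even N that reaches 0.90.

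The figure reproduces, with no allowance for cohorts.

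**2. What effect this is.** In a 2 × 2 layout the interaction test equals a t-test on the change from T0 to T1. With 23 per arm, the noncentrality is δ × √(23 × 23/46) = δ × √11.5. Setting this equal to √λ = √11.5 gives δ = 1.0 SD of the change.

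**3. Which correlation counts.** A stable difference between cohorts is present at both T0 and T1 and cancels in the interaction. What matters is the ICC of the change.

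**4. Assumed inputs.** 46 participants; 6, 8 or 12 clinic cohorts, half per condition, each treated as an independent unit; ICC of the change 0.02, 0.05 or 0.10. None of the cohort figures is in the article. Six is the smallest number that gives each of the three clinics both conditions.

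**5. Formulas.** With mean cohort size n = 46/J for J cohorts:

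- design effect DE = 1 + (n − 1) × ICC;
- cohort-level test: noncentrality √(11.5/DE), with J − 2 degrees of freedom;
- type I error of the participant-level test: by simulation with a random cohort effect on the change.

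Worked case, J = 8 and ICC = 0.05: n = 5.75; DE = 1 + 4.75 × 0.05 = 1.24; noncentrality √(11.5/1.2375) = 3.05; critical t on 6 df = 2.447; power 72%. The same design effect with 44 df would give 85%, so the degrees of freedom matter as much as the design effect.

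**6. Results** (ICC 0.02 / 0.05 / 0.10):

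| Cohorts | Mean size | Type I error of planned test, % | Power of cohort-level test, % | Same, ICC = 0, % |
|---|---|---|---|---|
| 6 | 7.7 | 6.7 / 9.1 / 12.8 | 67 / 60 / 52 | 72 |
| 8 | 5.75 | 6.0 / 7.7 / 11.1 | 77 / 72 / 64 | 80 |
| 12 | 3.8 | 5.8 / 6.7 / 8.6 | 84 / 81 / 77 | 86 |

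Repeat simulations moved the type I figures by less than half a point. The noncentral-t formula agrees with the power figures to about one point. At ICC = 0 the planned test holds 5% and has 91% power.

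**The case against.** The strongest reply is that the inflation is conditional, and that is right. It needs a positive ICC of the change, which the article does not give. There are grounds to expect a small one. Questionnaires are filled in before new content at each session, so at T1 the intervention group has had one session only. Patients choose their own one or two rules to practise. The day-clinic setting leaves the sleep routine largely in their hands. With 12 cohorts and ICC 0.02, the planned test is at 5.8%. A reader might infer that its p-values are certainly too small; the document does not support that.

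A reader might also put the whole power shortfall down to correlated outcomes. The last column of the table shows otherwise: with 6, 8 or 12 cohorts, power is already 72, 80 or 86% with no correlation, because few units leave few degrees of freedom. Nor does any passage say that a cohort shares one therapist. Section 2.1.1 says only that several professions deliver a standardised manual.

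It may be said that random effects belong in an analysis plan. That would answer a silence, but the article states both the two-factor model and the N derived from it, and neither matches the assignment it describes. The exploratory adjustment for sociodemographic factors and diagnoses does not address clustering. Nor does the non-parametric fallback, if it too treats patients as independent. Section 3.1 concedes possible seasonal and holiday effects, but as confounding, not as dependence within cohorts.

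**Conclusion.** The point holds in conditional form. Assignment is by cohort, while the analysis and the sample size are by participant. With any positive within-cohort correlation of the change, the planned test exceeds 5%: from about 5.8% (12 cohorts, ICC 0.02) to 12.8% (6 cohorts, ICC 0.10) over the range shown. The stated power of 0.90 is not what a test respecting the unit of assignment delivers. That test has about 52 to 84% power over the same range, and at most 86% with 12 cohorts even at zero correlation.

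The direction rests on the article's text. The size rests on assumed ICCs and cohort numbers. The power figures also rest on reading 0.25 as f with a correlation of 0.5, since the article itself says d. The model should be settled before the data are analysed, because choosing it after seeing the results would undermine the p-value.

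**What to change.** **Section 2.9.** Make the primary test of the T0 to T1 contrast a linear mixed model with a random cohort effect on the change and Kenward-Roger or Satterthwaite degrees of freedom, or an equivalent analysis of cohort means. Record a cohort identifier for each participant. Add clinic as a fixed effect only if the number of cohorts allows it, since three clinics take two further degrees of freedom.

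A permutation test over cohorts is no substitute with few cohorts. Four equally split cohorts give 6 arrangements (smallest two-sided p = 2/6 = 0.33) and six give 20 (2/20 = 0.10). It should be considered only from 8 cohorts upwards (70 arrangements, 2/70 = 0.03). Even then, strict alternation is not a random draw from those arrangements.

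**Section 2.4.** Restate the power at the planned N with the expected number of cohorts, a range of ICC, and both the design effect and the cohort-level degrees of freedom. The design effect alone would still overstate power, as the worked case shows (85% against 72%).

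**Cost.** Wording, one data field and a lower stated power, with wider confidence intervals. The change does not remove confounding by calendar time from the alternating allocation. Regaining 90% power would need more cohorts, which is a separate decision and not part of this fix.

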### Safety

2.10

There are no known risk factors associated with participation. Wearing an actigraph may cause temporary skin irritation or redness similar to wearing a watch. Participants are informed about any risk factors and encouraged to voice concerns regarding their participation during every step of the study. Concerns are documented.

## Discussion

3

To the best of our knowledge, to this day there is no intervention that targets transdiagnostic sleep problems in children and adolescents with psychiatric disorders in an easily implementable and short group design. This is the case despite extensive evidence demonstration the critical role adequate sleep and sleep quality play in physical and mental wellbeing. Studies have highlighted the negative effects of insufficient sleep on both physical health-such as cardiovascular health and physical fitness (Baranwal et al., 2023; Fonseca et al., 2021)—and even more so psychological health. For example, short sleep duration in young adults is associated with a higher risk to develop or intensify mental disorders such as anxiety, eating disorders, depression or bipolar disorders (Vestergaard et al., 2024). Conversely, adherence to guidelines for physical activity, screen time, and sleep duration has been shown to decrease the risk of the development of mental health problems in children. Notably adapting screen time and ensuring a sufficient sleep duration proved to be the most influential recommendation in prevention of mental health problems in this case (Sampasa-Kanyinga et al., 2020). Furthermore, as published in a recent pre-print by Harvey et al. (2025), variations of the sleep intervention TransS-C in a population with mental health problems significantly reduced sleep disturbances and daytime impairment while overall sleep health was increased. The intervention involving four or more sessions applicable mostly for individual, but also group setting, also improved overall psychiatric symptom severity. We hope to show similar effects while administering a shorter intervention complemented by the use of sleep logs and actigraphy as well as the metaphor tailored to the age of recipients.

Also, in children and adolescents, subjective sleep quality is not only a result of overall mental wellbeing, but there is a clear bidirectional association. Poor self-perceived sleep quality has been shown to increase the risk of anxiety, depression and stress symptoms later on (Zou et al., 2020). Especially in the context of changing sleep characteristics during adolescence, both sleep duration and quality seem to be crucial factors predicting later strain from mental health problems (Thompson et al., 2024; Tarokh et al., 2014). When taking a look at psychiatric samples it is even more evident that sleep problems occur comorbidly with many different psychiatric disorders such as ADHD, autism or depression (van der Heijden et al., 2018; Gupta et al., 2019). Sleep problems may even serve as a common thread linking various psychiatric disorders (Boafo et al., 2021). Diminished sleep quality can also interfere with treatment success of psychotherapy as well as symptom severity at discharge (Buysse et al., 1999; Boafo et al., 2021). Conversely, a reduction of sleep problems helps to improve the outcome of disorder-specific psychotherapy (Freeman et al., 2020). Summarizing the current evidence on the role of sleep in mental wellbeing, and considering the limited resources and options for mental health professionals for addressing sleep problems (Freeman et al., 2020), this underlines recurrent calls for transdiagnostic interventions targeting sleep (Vestergaard et al., 2024; Boafo et al., 2021; Tarokh et al., 2014). This may either be as a form of treatment or as prevention (Boafo et al., 2021). If proven to be efficacious, “Ready for Landing” aims to offer an option to answer those needs by providing a transdiagnostic, economic and easily implementable sleep hygiene intervention. It also seeks to provide knowledge about sleep and sleep hygiene to mental health professionals to sensitize for this matter as advised by Freeman et al. (2020). By improving sleep hygiene, sleep quality, and sleep duration it could therefor positively influence the bidirectional relationship between sleep disturbances and psychiatric disorders and contribute to improved psychological wellbeing in children and adolescents. Some studies propose sleep hygiene interventions to be a first line treatment when targeting sleep problems in the psychiatric context (Baranwal et al., 2023; Chung et al., 2018; Peach et al., 2016), while other studies suggest stand-alone sleep hygiene interventions are lacking substantial treatment effects in the treatment of sleep disorders like insomnia (Irish et al., 2015; Chung et al., 2018). Those studies underscore that if still implemented, sleep hygiene interventions should be done in a standardized and comprehensive delivery of content, rather than relying solely on brochures or psychoeducation. “Ready for Landing” addresses this by following the manual we seek to evaluate here, by incorporating elements from CBT-I, and by helping patients understand the functionality and necessity of sufficient sleep while encouraging them to build routines enabling them to improve their sleep related behaviors (Lin et al., 2018). The combination of CBT-I and its inherent elements of sleep hygiene education has further been proven to be efficacious (Hertenstein et al., 2022). Further by addressing both subjective sleep quality and objectively measured sleep duration the study aims to investigate the effect the intervention has on the parameters known to be influential on mental wellbeing (Vestergaard et al., 2024; Zou et al., 2020). It systematically evaluates the effects as demanded many times when talked about currently available sleep hygiene interventions (Nikles et al., 2020; McLay et al., 2024). If the effects are as proposed, “Ready for Landing” can be seen as an effective, theory-driven intervention to specifically target important domains of generic sleep problems.
